# **Enrollment**

The screening and enrollment of subjects will be done by a study coordinator or an investigator who is a member of the RELIEF research team within Vanderbilt or participating institutions. The study coordinator will be responsible for ensuring and reporting subject screening for study eligibility. Once the investigator has determined the subject’s eligibility for the study, the background of the proposed study and the benefits and risks of the study and procedures will be explained to the subject as a part of the consenting process. After consenting, subjects will be considered enrolled if they meet all the inclusion criteria and none of the exclusion criteria. Subjects who fail to meet any of the entry criteria will be excluded from the study and considered a screen failure. Screen failures will be recorded without patient information. Subjects will be able to withdraw from the study at any point.

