# **Data Collection**

The following data will be collected from the records:

1) Demographic data – age, gender, race, smoking status

2) Indication for chest tube placement

3) Date and time of catheter placement

4) Amount of daily fluid drained while in place

5) Imaging data (Chest x-ray and ultrasound images)

6) Length of hospitalization

7) Any instances of deviations from an assigned group (e.g. if a drain was thought clogged and

underwent saline flushing outside of the protocol)

8) Replacement of catheter secondary to dislodgement or inability to drain

9) Presence or absence of continuous wall suction application (for >75% of the previous 24 hours)

10) Date and time of catheter removal

11) Data related to daily chest tube blockage assessment and chest tube removal objective data.

(Because the study investigators and participants are not blinded to the study arm, specific objective criteria (see CRF) for chest tube removal due to successful pleural space infection management will be assessed on daily bases. These data will be documented to assess for change in the behavior of provider due to lack of blinding. This includes categorization of daily drain status, meeting either “successful,” “ongoing” or “”failed criteria.” This data will be used to perform sensitivity analysis to address the potential effects of blinding. Research team members will capture this data.

13) Imaging data on day of chest drain removal (ultrasound, chest-X-ray, or CT scan) characterizing effusion status (Table 2).

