Previous studies have shown a varying number of days to chest tube removal based on etiology, with a mean of 7.6 days (SD: 1.53) in no regular flush populations in a study of 98 patients with infected pleural space (Cafarotti). There is limited data with only one small study reporting median days to chest tube removal (5 days (3-7) in a study of 36 patients with no-flush strategy) (Horsley). Assuming a non-normal distribution, with data skewed to the right, we estimated a median of 6 days to chest tube removal. Assuming a difference of 1 day (24 hours), earlier chest tube removal in the intervention (6 days in the SOC group and 5 days in the intervention group) is a clinical meaningful difference to detect. The sample size is calculated from a two-sided Wilcoxon Rank-Sum test at a 0.050 significance level with a standard deviation of 1.5. Group sample sizes of 38 in each arm achieve 80% power to detect a median difference of 1. The sample size estimation is based on a 2000 Monte Carlo simulation assuming samples from a range of distribution such as Gamma, Lognormal, and Gumbel distributions. Assuming a 10% withdrawal rate and 15% intrapleural enzyme therapy failure (which can prevent reaching the primary endpoint), we plan to enroll 96 Participants (with randomization performed in a 1:1 ratio). To avoid an unbalance in randomization among groups, randomization will be stratified by intrapleural enzyme therapy use.

The main analysis for the outcome will be performed according to the intention-to-treat principle; all the participants with an observed outcome will be included in the analysis according to their assigned trial group.

*Analysis plans*

Continuous variables will be summarized using the mean (SD) or median (range), as appropriate. Frequencies and percentages will be used to summarize categorical variables. The student t-test or the Wilcoxon test will be used to compare continuous variables between two different groups. The chi-square test or Fisher’s exact test will be applied to assess the association between two categorical variables such as complications by treatment.

The Wilcoxon rank sum test will be used to compare time from randomization (within 24 hours of chest tube placement) until time to chest tube removal between two arms among patients who achieved successful chest tube removal.

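### The plan budgets a 10% withdrawal loss of the primary outcome and analyses only observed outcomes, although removal time is a routine record item that could mostly be kept

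*Protocol*

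**What the plan says.** - **Analysis population** (Protocol, Statistical Considerations). The main analysis is labelled intention-to-treat, but "all the participants with an observed outcome will be included in the analysis according to their assigned trial group".
- **Planned loss** (same section). The total of 96 is reached after "Assuming a 10% withdrawal rate and 15% intrapleural enzyme therapy failure (which can prevent reaching the primary endpoint".
- **Withdrawal.** Enrollment says "Subjects will be able to withdraw from the study at any point". Informed Consent/Authorization repeats the right to leave. Neither distinguishes a patient who wants flushing to stop from one who no longer allows the record to be used, and neither says whether chart data are still collected after withdrawal.
- **Source of the outcome.** Data Collection opens with "The following data will be collected from the records". Its list includes length of stay and, as item 10, the date and time of catheter removal, which is the end point of the primary outcome. Discharge date and further procedures are collected with the follow-up data.
- **Deviations.** Item 7 of the same list records departures from the assigned group.

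**The concern.** Adding 10% to enrolment for withdrawal makes sense only if withdrawn patients are expected to lack the primary outcome. Yet a patient who withdraws with the tube in place is normally still an inpatient, and the hospital will record when the tube comes out whether or not the flushes continue. Where permission to use the record remains, the loss is avoidable.

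Two things are at stake. The first is power, which is lost for no gain. The second is possible bias. The trial is open label, only the flush arm has a scheduled procedure every 6 ± 2 hours, and exposure to it grows with dwell time, which is the outcome. That is a conceivable route by which withdrawal could depend on both arm and outcome, and a complete-case population gives no protection against it. Outcomes that sites were never told to keep collecting cannot be restored later by an analyst or an SAP.

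**Working it through.** **Inputs** (Protocol, Statistical Considerations): "two-sided Wilcoxon Rank-Sum test at a 0.050 significance level with a standard deviation of 1.5"; 38 evaluable patients per arm for 80% power at a one-day difference; medians of "6 days in the SOC group and 5 days in the intervention group"; 96 enrolled, 48 per arm; allowances of 10% and 15%. The Wilcoxon efficiency of 0.955 relative to the t-test is an assumption.

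**1. The plan's own figures.**
- n per arm = 2 × [SD × (z0.975 + z0.80) / difference]² = 2 × [1.5 × (1.960 + 0.842) / 1]² = 35.3, so 36. Then 36 / 0.955 = 37.7, so 38. The stated 38 is reproduced.
- Enrolment: 38 × 1.25 = 47.5, so 48 per arm and 96 in total. This is reproduced, and it shows that the 10% is counted as lost outcomes alongside the 15%.

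**2. Outcomes available at 96 enrolled.**
- As planned: 96 × 0.75 = 72 (allowances added) or 96 × 0.90 × 0.85 = 73.4 (allowances multiplied).
- All withdrawn patients followed by chart, so that only the 15% failure allowance remains: 96 × 0.85 = 81.6.
- Difference: 81.6 − 72 = 9.6 or 81.6 − 73.4 = 8.2 outcomes. The planned withdrawal itself is 10% of 96 = 9.6 patients.

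**3. Power.** With m evaluable per arm, power = Φ{1 / [1.5 × √(2 / (0.955 m))] − 1.96}.

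| Situation | m per arm | Power |
|---|---|---|
| As planned, allowances added | 36 | 78.9% |
| As planned, allowances multiplied | 36.7 | 79.7% |
| Withdrawals recovered from chart | 40.8 | 83.7% |

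Wilcoxon simulation (10,000 runs, medians 6 and 5, SD 1.5) at 36 and then 41 per arm gives: normal 77.0% and 82.3%; gamma 78.5% and 83.6%; lognormal 80.8% and 85.2%; Gumbel 86.0% and 90.8%. The gain is 4 to 5 percentage points in every case. Put the other way, 38 / 0.85 = 44.7, so 45 per arm, or 90 in total, would suffice instead of 96.

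**4. Possible bias.** These simulations assume no true effect, 48 per arm, lognormal times with median 6 and SD 1.5, and the Wilcoxon test at a nominal 5%. Ten withdrawals are split between flush and control. The split and the mechanism are assumptions; the Protocol gives neither.

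| How flush-arm patients leave (control at random) | 7/3 | 8/2 | 10/0 |
|---|---|---|---|
| At random | about 5% | about 5% | about 5% |
| Probability proportional to dwell time | 5.0% | 5.4% | 6.0% |
| All from the slower half | 9.7% | 12.0% | 17.0% |

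The spurious benefit is 0.06 to 0.07 day in the proportional case (0.07 × 24 = 1.7 hours) and 0.25, 0.30 and 0.37 day in the slower-half case (6, 7 and 9 hours), against the 24 hours sought. With an equal 5/5 split, the slower-half mechanism gives 6.7%. A different steep assumption, with withdrawal in both arms weighted by the cube of the dwell-time rank, gives about 6% at 10% versus 10% withdrawal, about 10% at 15% versus 5%, and about 21% at 20% versus 0%. Marked inflation thus needs withdrawal to be both unequal between arms and strongly concentrated in slow drainers.

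**The case against.** The strongest reply is that no sentence ends data collection at withdrawal. A reader might infer that a patient who merely asks for the flushes to stop is removed from the trial, in breach of intention-to-treat. The document does not say that. Item 7 of Data Collection records departures from the assigned group, and analysis follows the assigned group, so the natural reading is that such a patient is a recorded deviation who stays in the arm. The population sentence would even include that patient if removal time is read from the chart. The 10% is a planning allowance, and the parenthesis about not reaching the endpoint attaches to enzyme-therapy failure. The consent pages are not in the review copy, and missing-data handling may sit in an SAP that is not shown.

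A reader might also infer that withdrawal is probably related to arm and that the primary result is therefore biased. No passage supports this. The larger error rates above follow from severe assumptions; the milder mechanism suggested by the design, more flushes to refuse as dwell lengthens, barely moves the type I error.

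These points stand and limit the claim. They do not remove it. The 10% inflation still treats withdrawn patients as having no outcome, the population rule is fixed in the Protocol, and nothing at hand tells sites to keep abstracting removal time after withdrawal.

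A further fair point is that the primary Wilcoxon or t-test is limited to successful removals. That selection is separate and has a larger allowance (15%), and nothing proposed here cures it.

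**Conclusion.** The point holds as an avoidable loss of primary outcomes, with bias as a possibility and not a demonstrated result. The firm cost is about 8 to 10 of 96 outcomes, and power of about 79-80% where about 84% by formula, or 85% in lognormal simulation, is available at the same enrolment. These figures assume that the 10% and 15% allowances are right and that every withdrawn patient still permits use of the record, so they are an upper limit on the gain. Bias requires withdrawal to depend on both arm and dwell time. Its size cannot be derived from the Protocol and ranges from negligible to material over the assumptions tried. The matter deserves correction because the change is cheap and data not collected cannot be recovered later.

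**What to change.** 1. In Enrollment and Informed Consent/Authorization, separate (a) stopping scheduled flushing or study assessments from (b) withdrawing permission to use the medical record. For (a), keep the participant in the assigned arm and take tube removal date, time and reason, discharge date, further procedures and death from the chart. Only (b) ends data collection.
2. In Statistical Considerations, define the main population as all randomised participants, and treat only those in (b) as missing. Where a time-to-event or competing-risk model is used, censor them at withdrawal. Censoring has no place in the Wilcoxon or t-test, so state how these patients are handled there.
3. Add a sensitivity analysis for informative loss, since censoring at withdrawal may itself be informative.
4. Address the restriction of the primary test to successful removals separately.

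The cost is a few sentences in the Protocol and consent form and minor chart abstraction, with no extra visits. Enrolment can stay at 96.

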# **Definitions**

A *complicated parapneumonic pleural effusion (CPPE)* is an effusion that has been infected with bacteria or other microorganisms (e.g., positive Gram stain or culture) or biochemical evidence of marked inflammation (e.g., low pH (<7.20), low glucose level (<60 mg/dl), and high lactate dehydrogenase (LDH)).

An *empyema* is a pleural effusion in which frank pus is aspirated from the pleural space.

A *blocked chest tube* is a chest tube that has stopped draining pleural fluid due to particulate material in the lumen of the tube.

A *successful chest tube removal* occurs when the infection in the pleural space has resolved as defined by clinical improvement of the patient and 24-hour fluid output from the chest tube of 150 mL or less.

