# **Outcomes**

Primary outcome: time from randomization (within 24 hours of chest tube placement) until time to chest tube removal (hours).

Secondary outcomes:

1 – length of hospitalization.

2 – radiographic improvement as evidenced by chest x-ray at the time of chest tube placement compared to the time of removal.

3 – additional surgical procedures for the management of pleural space infection (VATS, additional drains, etc.).

4 – Complications.

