# **Statistical Considerations**

*Objective and sample size justification*

This is an open label, randomized, multicenter study of the application of flushing for the treatment of pleural space infection among hospitalized patients requiring chest tube drainage. Patients will be enrolled and randomized with a 1:1 ratio to two treatment groups: (1) 20 mL of sterile saline catheter flushing every 6±2 hours with the application of continuous -20 cm H2O suction (2) as needed saline flushing for blockage with the application of continuous -20 cm H2O suction. After enrollment, daily drain patency and criteria for drain removal will be measured and documented. The primary objective of this study is to evaluate the impact of regular chest tube drain flushing on the length of time to catheter removal for patients admitted with pleural space infection who require thoracostomy for their management. Chest tube removal due to chest tube dislodgement or malposition, or “kinking”, and if the patient is deceased with a chest tube in situ, are considered competing risks and will be analyzed as such.

The secondary objective of this study is to evaluate the impact of regular chest drain flushing on the length of hospitalization for patients, radiographic improvement on chest imaging, the need for additional pleural interventions, and associated complications of chest tube management.

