For the primary endpoint, if data is normally distributed, data will be analyzed via students t-tests comparing time from randomization until time to chest drain removal between the two arms, among patients who received successful chest drain removal. For non-normally distributed data, the Wilcoxon rank sum test will be used for this comparison. If a chest drain’s removal was due to a competing risk (chest drain dislodgement, malposition or “kinking”, patient died with chest drain in situ), a competing risk time-to-event regression model will be applied.

In addition to the primary endpoint of interest, we are interested in the comparison of the time to the failure of therapy/drainage between two arms. For the time to the failure of therapy/drainage analysis, Cox regression with the adjustment of covariates of interest will be used in all enrolled subjects, including patients who reached successful chest tube removal and those with failure of therapy/drainage and need for additional interventions. The cumulative failure of therapy/drainage curve will be calculated from the Kaplan-Meier method and compared using the log-rank test. For the exploratory study, we will apply Markov ordinal longitudinal proportional odds state transition model to analyze our interventions into impact on the process of chest tube drainage to successful outcome or failure. This model will provide further characterization of intervention and control arms with regards to state of chest drain and state of patient among all populations, including those with chest drain failure, to characterize differences among these groups.

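### The primary test is limited to patients whose tube was successfully removed, a post-randomisation subset, so it is not an intention-to-treat comparison and is biased if failure rates differ by arm

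*Protocol*

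**What the plan says.** The Outcomes section gives: "Primary outcome: time from randomization (within 24 hours of chest tube placement) until time to chest tube removal (hours". It does not limit removal to successful removal.

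Statistical Considerations promises that "The main analysis for the outcome will be performed according to the intention-to-treat principle", and then glosses this as "all the participants with an observed outcome will be included in the analysis according to their assigned trial group".

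The analysis plans narrow the population twice. The Wilcoxon comparison is of time "until time to chest tube removal between two arms among patients who achieved successful chest tube removal". The paragraph on the primary endpoint repeats the limit for the t-test or Wilcoxon test: "between the two arms, among patients who received successful chest drain removal". Under Definitions, success "occurs when the infection in the pleural space has resolved as defined by clinical improvement of the patient and 24-hour fluid output" of 150 mL or less, so it is assessed during follow-up.

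The competing risks are dislodgement, malposition, kinking, "and if the patient is deceased with a chest tube in situ, are considered competing risks". Treatment failure, defined under the Multistate Transition Model as needing an additional pleural procedure, is not listed. The sample size allows 15% for failure of intrapleural enzyme therapy, on the ground that it can prevent a patient reaching the primary endpoint.

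Failures are analysed elsewhere. Cox regression and a log-rank test of time to failure cover all enrolled subjects, in addition to the primary endpoint, and an exploratory Markov model includes patients with drain failure.

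**The concern.** Randomisation makes the arms comparable at entry. It does not make the successes in one arm comparable with the successes in the other if treatment affects who succeeds. The Hypothesis section expects flushing to prevent surgery and additional drains, so the plan selects its analysis set on a variable the intervention is meant to move.

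Suppose flushing rescues some difficult patients who would otherwise fail, and they drain for a long time first. They enter the flushing arm's success group with long times, while their counterparts in the control arm disappear as failures. Flushing then looks slower than it is. If flushing caused failures, the distortion would favour it. Even where failure is unrelated to drainage speed, the test gives no credit for preventing failure.

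**Working it through.** **Plan's own figure.** Inputs from Statistical Considerations: two-sided alpha 0.05, power 80%, difference 1 day, SD 1.5 days, Wilcoxon test.
- t-test size per arm: 2 × (1.5 × (1.960 + 0.842) / 1)² = 35.3, so 36.
- Divided by the Wilcoxon relative efficiency 3/π = 0.955: 36 / 0.955 = 37.7, so 38 per arm. This agrees with the plan.
- Simulated Wilcoxon power at 38 per arm, medians 6 and 5: gamma 0.81, lognormal 0.83, Gumbel 0.88.
- Enrolment: 38 × 1.25 = 47.5, so 48 per arm and 96 in total. The 25% is 10% withdrawal plus 15% failure, so the 80% power was computed for a comparison without failures.

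**Who is analysed.** A patient whose tube is taken out after failed drainage has an observed removal time under the Outcomes definition. That patient satisfies the gloss on intention-to-treat but is excluded by both analysis sentences. The competing-risk regression does not bring the patient back: failure is not a listed event, the model is invoked only when a listed event occurs, and it is not said to replace the t-test or Wilcoxon test.

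**Size of the bias.** Both models use 48 × 0.9 = 43 patients per arm after withdrawal, control median 6 days and SD 1.5. The 15% control failure comes from the sample-size paragraph. The 33% echoes the Background statement that about one-third of patients need surgical drainage. The other failure rates and the link between failure and slowness are assumptions.

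*Model A: lognormal times, with failure linked to slowness through a latent correlation rho from 0 to 0.9.*

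| Failure, control vs flushing | True time gain | Success-only test | All patients, failures ranked worst |
|---|---|---|---|
| 15% vs 5% | none | false harm 2–10% | – |
| 33% vs 15% | none | false harm 3–22% | – |
| 33% vs 15% | 0.5 day | power 8–28% | power 46–66% |
| 15% vs 5% | 1 day | harm 0%, power 77–85% | power 88–92% |

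False harm means flushing declared significantly slower; the nominal rate is 2.5%. In one run of 1,000 trials per scenario, the first row was 1.7%, 4.0%, 4.8% and 10.3% at rho 0, 0.3, 0.6 and 0.9. The Monte Carlo standard error at 2.5% is √(0.025 × 0.975 / 1000) = 0.5 points, so 1.7% is compatible with the nominal rate.

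*Model B: gamma times; patients rescued from failure by flushing succeed late, at a median of 9 days.*

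| Failure, control vs flushing | True gain in the others | Success-only medians, control vs flushing (days) | Success-only test | All patients, failures ranked worst |
|---|---|---|---|---|
| 15% vs 15% | none | 6.00 vs 6.00 | false harm 2.7% | 2.3% |
| 15% vs 5% | none | 6.00 vs 6.21 | false harm 8.8% | 1.5% |
| 30% vs 10% | none | 5.99 vs 6.52 | false harm 25.6% | 0.5% |
| 30% vs 10% | 0.25 day | 5.99 vs 6.28 | false harm 11.0% | 0.3% |
| 15% vs 5% | 1 day | 6.01 vs 5.22 | power 43% | power 66% |

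In the last row the 1-day gain shows as 6.01 − 5.22 = 0.79 day.

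**Opposite direction.** With 5% failure in control and 15% with flushing (lognormal, correlation 0.7, no time effect), the success-only test falsely favoured flushing in 7.1% of trials.

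**The case against.** The restriction looks deliberate and has some internal logic. The hypothesis is about earlier successful removal, success is defined, intention-to-treat is qualified to observed outcomes, and the sample size budgets for failures. The Cox, log-rank and Markov analyses, together with the secondary outcome on additional procedures, would show a difference in failures beside the primary result. This shows that the protocol does not ignore failures. It does not make the primary comparison a randomised one, because none of those analyses is primary and they address a different endpoint.

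A reader might infer that the plan would turn a benefit of flushing into apparent harm. The documents do not support that as the expected result. At the planned 1-day gain with 15% versus 5% failure, neither model reverses the sign. In Model B a true time gain came out as apparent harm at 30% versus 10% failure, with a gain of only 0.25 day and every rescued patient draining late. That is a possibility under harsh assumptions, not a forecast.

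The size of the bias is also uncertain. It depends on how strongly failure tracks slow drainage, which the protocol does not give; at zero correlation the false-harm rate stays near nominal. This objection stands, and it is why ranges are given.

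A reader might also infer that tubes replaced for inability to drain are dropped. The protocol records replacement but does not classify it as failure, so the point does not rest on it.

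**Conclusion.** The concern holds. The primary analysis conflicts with the stated outcome and with the intention-to-treat promise, even as that promise is qualified, and it conditions on a post-randomisation state that treatment is expected to alter. Bias requires failure rates that differ by arm and failures concentrated in slow-draining patients. If both hold and flushing has no effect on time, false significant harm rises from the nominal 2.5% to as much as about 10% (15% versus 5% failure) or 22% (33% versus 15%). With true gains of 0.25 to 1 day the main consequence is attenuation and lost power: at 0.5 day and 33% versus 15% failure, 8–28% against 46–66%. At the planned 1-day gain with 15% versus 5% failure, success-only power ranges from 43% to 85% across the two models, with no reversal. Equal failure of the same kind of patient in both arms gives no bias. Because a significant result in either direction could reflect selection, this should be corrected before analysis.

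**What to change.** In both analysis sentences, replace the success-only restriction with all randomised patients by assigned arm, and reword the intention-to-treat sentence to match.

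- **Preferred:** make the primary analysis the cumulative incidence of successful removal from randomisation. Add treatment failure to the listed competing events (dislodgement, malposition, kinking, death in situ), and censor withdrawals and patients discharged with the tube in place. This stays closest to the plan, which already names a competing-risk model.
- **Alternative:** keep the Wilcoxon test, ranking treatment failure and death after all successes. Handling of withdrawals and mechanical tube losses must then be stated; mechanical losses need not be merged with treatment failure.

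Keep the success-only comparison as supportive.

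Removal times, reasons and additional procedures are already collected, so no new data are needed. The cost is in power: the 80% applies to success-only times and must be restated. For the ranked Wilcoxon version, power for a 1-day gain is roughly 60–80% with equal 15% failure, and roughly 65–90% if flushing lowers failure to 5%, depending on the failure model. Holding 80% in the equal-failure case may require more patients.
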